## **6.2 Subject Exclusion Criteria**

The following will exclude potential subjects from the study:

1. erythrodermic, predominantly guttate, exclusively palmar/plantar or generalized pustular psoriasis;
2. current drug-induced or aggravated psoriasis (*e.g.* a new onset of psoriasis or an exacerbation of psoriasis from beta-blockers, calcium channel blockers, or lithium carbonate);
3. use of the following concurrent systemic medications: corticosteroids, retinoids, cyclosporine, methotrexate or biologic agents. The wash out period for all these medications is 4 weeks or 5 half-lives prior to baseline, whichever is longer.
4. use of concurrent topical medications (must be discontinued at least 2 weeks prior to baseline);
5. UVA or UVB therapy within 4 weeks of baseline;
6. the presence of uncontrolled hypertension, uncontrolled diabetes, clinically significant (uncontrolled) cardiovascular disease, uncontrolled asthma or reduced pulmonary capacity or a history of seizure or other neurologic disorder;
7. presence or history of paresthesia or neuropathy;
8. abnormalities on neurologic exam at screening or baseline;
9. clinically significant ECG abnormalities in the opinion of the Investigator;
10. history of any cancer requiring systemic chemotherapy or radiation; individuals with a history of non-melanoma skin cancer, nonrecurring carcinoma in situ treated with laser or cryotherapy or cervical cancer-in-situ, resected surgically with no evidence of disease, may be accepted on a case by case basis at the discretion of the Investigator;
11. the presence of acute infection or history of acute infection as judged by the Investigator within 7 days of baseline; additionally, oral temperature may not exceed 37.4° C at baseline;
12. the presence of clinically significant laboratory abnormalities (chemistry panel of 20 analytes [Chem-20; fasted at least 4 hours], complete blood count [CBC], and urinalysis [UA]) as determined by the Investigator;
13. a positive hepatitis screen (Hepatitis BsAg or anti-HCV) or positive Human Immunodeficiency Virus (HIV) antibody test;
14. history of treated or untreated TB
15. any history of anaphylaxis that is important in the view of the Investigator;
16. participation in another clinical trial with receipt of an investigational product within 90 days of baseline (or 5 half-lives of the previous drug, whichever is longer);
17. history of alcohol abuse that is important in the view of the Investigator;
18. positive drug screen for amphetamines, barbituates, benzodiazepines, cocaine,

cannabis, methamphetamine, methylenedioxymethamphetamine, opiates or phencyclidine

19. inadequate venous access that would interfere with obtaining blood samples;
20. positive pregnancy test at screening or at baseline or current lactation (female subjects only);
21. inability or unwillingness to comply with study restrictions, return for follow up appointments, or other considerations, in the opinion of the Investigator, which would make the candidate unsuitable for study participation.

### **6.3 Subject Withdrawal Criteria**

Subjects who meet all the inclusion criteria and have none of the exclusion criteria will be eligible to be enrolled into the study.

Subjects will be informed that they are free to withdraw from the study at any time and for any reason. The Investigator may remove a subject from the study if, in the Investigator's opinion, it is not in the best interest of the subject to continue the study. Subjects may be withdrawn if there are applicable safety or tolerability concerns on the part of the Investigator. Additionally, withdrawal of an individual subject will occur if any one of the following are met:

- Occurrence of an adverse event of Grade 3 or higher (CTCAE v4.0)
  - Grade 3 and greater laboratory abnormalities, that are
    - reproducible and sustainable (repeat laboratory test performed within 24-36 hours), and
    - clinically significant (according to the Investigator's discretion),
  - Grade 3 AEs that are clinically significant but clearly not related to study drug will be considered individually for withdrawal by the investigator, based on the clinical picture and logistical ability to manage the subject.
- Occurrence of a serious adverse event (SAE)
- Development of paresthesia/peripheral neuropathy symptoms that do not resolve prior to the next dose (at the discretion of the Investigator).

Notification of discontinuation will be made immediately to the Sponsor. In case of premature discontinuation of study participation, efforts will be made to perform all final study day assessments. The date the subject is withdrawn from the study and the reason for discontinuation will be recorded on the subject's Case Report Form (CRF). All dropouts will be followed until the resolution of all their AEs or until the unresolved AEs are judged by the Investigator to have stabilized.

Subjects that withdraw after receiving study drug will not be replaced. Subjects that withdraw prior to receiving study drug will be replaced and will receive a new study number.

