## **12 ASSESSMENTS OF IMMUNOGENICITY**

### **12.1 Immunoassay – Anti-Drug Antibody**

Serum samples will be collected from each study subject pre-dose on Day 1, on Day 15, Day 29 and End of Study. Serum will be evaluated for binding ADA using an ELISA-based method. Each positive serum sample will be evaluated for ADA specificity by repeating the ELISA in the presence of an excess of ShK-186. Confirmed positive, specific serum samples will be titered by serial dilution, and a numerical titer will be assigned.

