## 14 STUDY PROCEDURES

### 14.1 Evaluations

Evaluations are summarized in [Appendix A](#). A central laboratory will perform all laboratory evaluations with the following exceptions:

- PK plasma sample analysis will be performed by Chimera Biotech;
- ADA evaluations will be performed by Kineta, Inc.;
- Plasma sample analysis for biomarkers by Luminex and Singulex will be performed by Myriad Genetics Inc. and the [name] laboratory (Rockefeller University), respectively;
- Skin biopsy samples will be processed and analyzed for histology, immunohistochemistry and gene expression by the [name] laboratory (Rockefeller University);
- Immunophenotypic evaluation of T cell subsets in PBMC samples will be performed by Kineta, Inc.;
- TEMPUS tubes with whole blood will be processed for RNA and evaluated by QPCR by Kineta Inc.

Every attempt will be made to perform evaluations on the scheduled day and time, as appropriate. Evaluations scheduled to occur on dosing days should be performed within the following post-dose intervals:  $5\pm 1$  min,  $15\pm 5$  min,  $30\pm 5$  min,  $1h\pm 10$  min,  $2h\pm 15$  min and  $4h\pm 15$  min. All of the post-dose procedures should be timed according to the time of dose administration. Evaluations scheduled to occur on non-dosing days through Day 29 should be performed on the day of the scheduled visit. Visits scheduled for beyond Day 29 should be performed within 1 day of the scheduled visit. Deviations from these times should be recorded in the CRF. Missed doses or significant alterations to the timing of a dose are permitted with the prior approval of the Sponsor.

A PPD or QuantiFERON-TB Gold test and chest X-ray will be performed at screening if it was not done within 6 months of Baseline (Day 1). PPD will be performed using 5 tuberculin units (5 TU). Reading will be performed 48 to 72 hours after PPD injection. An induration of 5 mm or more will be considered as positive. If the QuantiFERON-TB Gold test is chosen, it will be performed according to the manufacturer's instructions. Subjects who demonstrate evidence of latent TB infection (either PPD more than or equal to 5 mm of induration or positive Quantiferon Gold, irrespective of BCG vaccination status and negative CXR findings for active TB, and/or suspicious CXR findings) will not be allowed to participate in the study.

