#### **14.1.9 End of Study Evaluations and Procedures (Day 57)**

The following procedures will be performed at the End of Study visit:

1. interim medication/medical history;
2. routine physical examination (including neurologic exam);
3. vital signs (including temperature, respiratory rate, and supine blood pressure and pulse);
4. AE evaluations;
5. patient and Investigator global assessments of psoriasis;

6. patient quality of life assessment (DLQI);
7. patient assessment of disability (PDI);
8. %BSA, Psoriasis Area and Severity Index (PASI) and target lesion assessments;
9. plasma sample for study drug concentration;
10. clinical laboratory evaluations (including Chem-20, CBC, and UA);
11. whole blood collection for biomarkers: PBMCs, plasma, serum and whole blood sample for RNA (TEMPUS™);
12. photographic documentation of target lesion that has been assessed throughout, biopsied lesion(s), as well as psoriasis-involved body areas (Subjects will be instructed to abstain from the use of emollients for 24 hours prior to the scheduled photography);
13. serum sample for assessment of antibodies to ShK-186;
14. serum pregnancy test (female subjects only);

Subjects that prematurely discontinue from study should complete all assessments for the scheduled visit and all End of Study assessments.

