#### 14.5.2 Recording Adverse Events

An AE is defined as any untoward medical occurrence experienced by a patient or healthy subject, whether or not considered drug related by the Investigator. A treatment emergent AE is an AE that is reported after a dose of study drug.

Adverse events/experiences are all:

- unfavorable changes in general condition;
- subjective or objective signs/symptoms;
- concomitant diseases or accidents;
- clinically relevant adverse changes in laboratory parameters observed in a subject in the course of a clinical study.

Adverse events/experiences comprise all disturbances of general health status, subjective and objective disease symptoms (including laboratory abnormalities), and accidents observed in the context of a clinical trial, irrespective of a possible causal relationship with the administration of the trial substance. Events occurring in the framework of a clinical trial during drug-free, and post-study drug periods, under placebo, or in a reference group receiving drug or non-drug therapy, are also to be designated as AEs.

All AEs, whether volunteered, elicited, or noted on physical examination, will be recorded throughout the study (*i.e.*, from the time of first injection on Day 1 until End of Study).

The severity of AEs that are clinical abnormalities, vital signs, and systemic issues will be

categorized according to the criteria presented in the Common Terminology Criteria for Adverse Events v4.0.

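### Section 6.3 takes subjects with its safety triggers out of the study, not only off study drug, so they have fewer scheduled immunogenicity and laboratory samples than the others

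*Protocol*

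**What the plan says.** **Triggers.** Protocol section 6.3 states that "withdrawal of an individual subject will occur if any one of the following are met". The triggers divide as follows.

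- Mandatory: a serious adverse event, related or not; a Grade 3 adverse event that is not clearly unrelated to drug; any adverse event of Grade 4 or higher. Laboratory abnormalities count only if they are reproducible and clinically significant.
- Left to the Investigator: paresthesia or neuropathy not resolved by the next dose, and Grade 3 events clearly unrelated to drug.

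**What the subject leaves.** The same section goes on: "The date the subject is withdrawn from the study and the reason for discontinuation will be recorded". It also speaks of ending study participation and of dropouts.

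**What is provided afterwards.** Section 6.3: "In case of premature discontinuation of study participation, efforts will be made to perform all final study day assessments", and "All dropouts will be followed until the resolution of all their AEs" or until they have stabilised. Section 14.1.9: "Subjects that prematurely discontinue from study should complete all assessments for the scheduled visit and all End of Study assessments". Neither section gives a day for that set.

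**The schedule that other subjects follow.** Section 12.1: "Serum samples will be collected from each study subject pre-dose on Day 1, on Day 15, Day 29 and End of Study". Appendix A puts safety laboratory tests after Day 1 on Days 8, 15, 22, 29 and 57, and a complete neurological examination on Day 57. Section 14.5.2 records adverse events "from the time of first injection on Day 1 until End of Study".

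**The concern.** The primary objective is safety, tolerability and immunogenicity. Under section 6.3 the subjects with the most serious safety experience are the ones whose scheduled observation stops early. Blood that was not drawn and events that were not asked about cannot be recovered in the analysis.

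Subject protection requires that dosing stops. It does not require that observation stops. The adverse event triggers are also not confined to the dosing period: a serious adverse event during follow-up, after the last dose on Day 29, calls for withdrawal although no drug is left to stop. Only the paresthesia criterion is tied to a next dose.

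**Working it through.** **1. Study or study drug?** Section 6.3 introduces the triggers directly after text on removing a subject from the study, and then records the date of leaving the study. Section 14.5.3, on pregnancy, stops only the treatment portion. The protocol therefore has treatment-only wording and does not use it in 6.3.

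**2. When is the End of Study set done?** Two readings are possible.

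- *Exit reading:* section 14.1.9 joins the set to the current visit, which suggests that it is done on leaving.
- *Day 57 reading:* the synopsis (study period), Figure 1 and the heading of 14.1.9 all tie End of Study to Day 57.

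The text does not settle this, so both are counted.

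**3. Antibody samples after the first dose** (planned: Days 15, 29 and 57, so 3). Count the scheduled samples up to and including the exit day, then add the End of Study set. At exit, the set coincides with any sample due that day.

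| Exit day | Set at exit | Set on Day 57 |
|---|---|---|
| 4, 8, 11 | 1 | 1 |
| 15 | 1 | 2 |
| 18, 22, 25 | 2 | 2 |
| 29 | 2 | 3 |

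Exit on Days 4 to 11 leaves 1 of 3 on either reading. On the exit reading that sample also falls before Day 15, the first post-dose time that the protocol chose.

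**4. Safety laboratory tests.** Example, exit on Day 15: Days 22, 29 and 57 are missed on the exit reading; Days 22 and 29 on the Day 57 reading.

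**5. New adverse events, exit reading only.** Days between exit and Day 57: 57 − 4 = 53; 57 − 15 = 42; 57 − 29 = 28. On the Day 57 reading nothing is lost here.

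**6. Complete neurological examination, exit reading only.** Doses are 3 or 4 days apart. A subject who exits at the next dosing visit, before dosing, has the last complete examination 3 to 4 days after the last dose. For a completer it is 57 − 29 = 28 days.

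**7. How many subjects?** Section 3.3 reports no serious adverse event and no event of Grade 3 or higher in either earlier healthy-volunteer study. Each had 4 cohorts × 6 active = 24 subjects, 48 in all. The active arms here hold 24 × 10/12 = 20. With zero events, the upper limit of the exact two-sided 95% interval is 1 − 0.025^(1/n).

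| Basis | n | Upper limit | × 20 |
|---|---|---|---|
| Both studies | 48 | 7.4% | 1.5 |
| Repeat-dose study | 24 | 14.2% | 2.8 |
| Repeat-dose study, 30 and 60 µg only | 12 | 26.5% | 5.3 |

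These are ceilings, not expectations. They carry healthy-volunteer rates over to patients and leave out the discretionary triggers.

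**8. Weight of one subject.** The arms are 24 × 5/12 = 10, 10 and 24 × 2/12 = 4, and dosed subjects are not replaced. One withdrawal is 10% of an active arm or 25% of placebo. In precision terms the change is small: with no late events in an active arm, the one-sided 95% upper bound 1 − 0.05^(1/n) goes from 25.9% (n = 10) to 28.3% (n = 9).

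**The case against.** Withdrawal with an exit assessment and follow-up of adverse events is a coherent rule for a four-week Phase 1b study with 24 subjects and descriptive safety summaries. Few or no subjects may be affected, and no planned analysis becomes wrong. Pregnancy has its own need for outcome tracking, so its treatment-only wording does not prove an error in 6.3. Other safeguards exist. Section 14.1 allows work-up such as nerve conduction studies when symptoms persist off therapy, section 14.2.5 allows symptom-directed neurological examinations, and section 14.2 says that all treated subjects are assessed for safety. Where a trigger is discretionary, the Investigator can keep the subject, because "Missed doses or significant alterations to the timing of a dose are permitted with the prior approval of the Sponsor".

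Most of this stands and limits the size of the point. It does not remove it. The safeguards are symptom-driven or general, and none keeps the scheduled antibody and laboratory samples after withdrawal.

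Three stronger readings are tempting and are not supported:

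- *That new adverse events after exit certainly go unrecorded.* This holds only on the exit reading. The protocol mostly uses End of Study for Day 57, and section 14.5.2 counts events in drug-free and post-drug periods as adverse events.
- *That every trigger is automatic.* Unresolved paresthesia and clearly unrelated Grade 3 events are for the Investigator to judge.
- *That withdrawn subjects are abandoned.* Existing events are followed and one full assessment set is provided.

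**Conclusion.** The point holds in limited form. Section 6.3 ends study participation where stopping study drug would protect the subject equally well. Whichever day the End of Study set is done, exit on Days 4 to 11 leaves 1 of 3 post-dose antibody samples, and the scheduled safety laboratory tests between exit and Day 57 are not taken. The further loss of the Day 57 antibody sample, laboratory tests and complete neurological examination, and of new adverse events up to Day 57, depends on the set being done at exit and ending the subject's study.

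The number affected is unknown and may be zero. The concern is less about precision than about which subjects have incomplete data on the primary objective: those with the most important safety events. The change should be made because it is cheap and has to be in place before any such subject leaves.

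**What to change.** In sections 6.3 and 14.1.9:

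- Reword the criteria as discontinuation of study drug, with the triggers unchanged.
- State that the early assessment set is done at discontinuation.
- State that, unless consent is withdrawn, the subject attends the remaining planned key visits without dosing: at least Day 15 and Day 29 if not yet reached, and Day 57. These visits cover antibody sampling, safety laboratory tests and adverse event inquiry, with the complete neurological examination on Day 57.
- State that all adverse events are recorded to Day 57.

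A subject who stops on Days 4 to 11 then has the set at discontinuation plus all 3 planned antibody samples. Laboratory tests on other days, such as Days 8 and 22, are not restored and stay at the Investigator's discretion.

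The cost is wording in two sections and, for each subject concerned, up to three visits that were already planned: three after stopping on Days 4 to 11, two after Days 15 to 25, one after Day 29. Sample size and drug exposure do not change.

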### **6.4 Study Discontinuation**

The entire study may be discontinued by the Sponsor at its own discretion and for any reason, such as:

- unacceptable safety or tolerability experience;
- medical or ethical reasons affecting the continued performance of the study;
- difficulties in the recruitment of subjects;
- cancellation of drug development.

## **7 TREATMENT OF SUBJECTS**

### **7.1 Description of Study Drug**

See Section 9.

### **7.2 Concomitant Medications**

Excluded systemic medications should be discontinued at least four weeks prior to baseline or five half-lives, whichever is longer.

Topical medications should be discontinued at least two weeks prior to baseline.

Subjects will refrain from participation in another clinical trial with receipt of an investigational product within 90 days of baseline (or 5 half-lives of the previous drug, whichever is longer).

Other agents for the treatment of psoriasis should not be added without prior approval of the Investigator.

### **7.3 Treatment Compliance**

Study drug will be administered at the clinical site by trained study staff.

### **7.4 Randomization and Blinding**

This will be a double-blind, placebo-controlled study. As such, except for the specifically designated unblinded study site clinical and ancillary staff, the Investigator and remaining study site clinical staff will be blinded as to treatment. One or more members of the study site clinical and ancillary staff will remain unblinded during the entire study. These unblinded study site staff will not be involved in any on-study data collection or subject evaluation (*i.e.*, will be only allowed to perform activities such as test material receipt, storage, and handling; unit dose preparation; and/or shipment of laboratory samples).

The original treatment randomization list will be kept secured from the Investigator or Investigator staff until the database is finalized and hard locked. In case of medical emergency (*i.e.*, an adverse reaction that necessitates identification of the test material for the welfare of that subject), the Investigator should contact the Medical Monitor. The Investigator will also have access on site to the randomization code provided by the Sponsor, if the Investigator cannot contact the Medical Monitor. In a safety related event, the Medical Monitor and Sponsor may be unblinded to a subject's treatment in order to assess the event and reporting of the event. The Sponsor must always be notified prior to breaking the blind, EXCEPT in a life-threatening emergency. In these instances, emergency code breaks must be reported to the Sponsor as soon as possible. The time when the study blind was broken, by whom, and the reason why must be documented in the source document and the electronic Case Report Form (eCRF).

Except in a medical emergency, the Investigator or designee and blinded study site clinical staff will remain blinded during the conduct of the study and until such time as all discrepancies in the clinical database are resolved (*i.e.*, at the time of the database lock).

The Investigator will remain blinded as to treatment, for purposes of safety and tolerability data review.

Additionally, study monitors, data management, statisticians, and sponsor or sponsor-contracted personnel involved in review of subject data will remain blinded. Certain designated staff at

CRO and a separate study monitor will be involved in managing study drug and verifying drug accountability and therefore will not be blinded.

## 8 STUDY DRUG MATERIALS AND MANAGEMENT

### 8.1 Drug Product and Placebo

ShK-186 is presented as a single-use, preservative-free 0.65 mL vial at a strength of 1 mg/mL.

The formulation buffer contains water for injection, sodium phosphate (10 mM), sodium chloride (0.8%), and Polysorbate 20 (0.05%) at pH 6.0. All excipients meet USP compendial requirements and are not of animal origin.

Prior to administration, the drug product will be diluted by an unblinded member of the study site staff in normal saline for injection to achieve the appropriate concentration for a final administered volume of 0.3 mL. Normal saline to be used for the dilution is the saline used as placebo. More detailed information on the preparation of dosing solutions is presented in the Study Manual.

The Sponsor, or designee, will provide the Investigator with adequate quantities of the study drugs (see [Table 2](#)).

Placebo will be Normal Saline Solution for injection provided by the CRO and prepared by an unblinded member of the study site staff.

